**Participation and consent**

Based on their assigned arm, participants will then be directed to research assistants who will deliver the allocated intervention. Participation in the study will be voluntary and anonymous. Access to other vaccination and medical services in the health center will not be affected in any way because of the participation in the study. Participants will be able to withdraw from the study at any time without giving any explanations.

All participants will be asked to complete a baseline survey after the consent. The questionnaires will collect information about their sociodemographic information, vaccine-related attitudes and behavior, pro-social intention and behavior, and their intended donation to support vaccination of other individuals (pay-it-forward arm only). We will add caregivers’ WeChat account for future follow-up and publicizing the microdonations and transparency.

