**Randomization and treatment allocation**

The research assistants will explain on-site the trial purpose, procedures, expected benefits and possible risks to participants, and obtain written consent to participate in the trial. Research assistants will then randomize participants into standard-of-care and pay-it-forward arms using a sealed envelope method. The envelope includes a random numerical ID generated using SPSS 21.0 that corresponds to the assigned arm (standard-of-care or pay-it-forward), a QR code for an online questionnaire survey, and postcard messages (pay-it-forward arm only). After receiving the allocated treatment, participants who agree to receive a vaccine will make an appointment through our trial and we will link them with a community health staff member who helps coordinate the administration of vaccination at the center.

We will use an information tracking sheet to record the assigned treatment, collect information about age (verified by identification card on-site), numerical ID and contact information. Personal information will be used for arranging clinical visits only and will not be accessible to staff who are not involved in the recruitment and clinical arrangement process.

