**Blinding**

In a behavioral intervention, both participants and people who deliver the treatment know which treatment they are receiving, and it is impossible to conduct a blind trial. But we will adopt several blinding techniques during the process to minimize biases. First, our trial will use an envelope concealment method. The process of generating the sequence of random digits and assembling envelopes is confidential to all on-site research assistants who recruit participants. Second, the allocated intervention will be concealed from study participants and research assistants onsite prior to assignment until they open the envelope. Second, the community health staff coordinator will not know which treatment a participant receives but only help coordinate within the clinic for administering the vaccination after the intervention delivery. Third, both the research assistants and/or community staff coordinator will help collect handwritten messages/donations, but they will be trained to maintain a high degree of consistency and neutrality in the process. Fourth, the allocated intervention (pay-it-forward or standard-of-care) will be blinded to physicians who prescribe an HPV vaccine throughout the process. Finally, the outcome assessors will be blinded from the knowledge of which intervention a participant receives.

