**Outcome measures**

*Primary outcome*

The primary outcome of the study will be first-dose HPV vaccine uptake in each arm after the intervention as assessed by administrative records. The choice of HPV vaccines will be dependent on the availability of vaccine products at the selected community health centers, primarily 2v-HPV vaccines.

*Secondary outcomes*

Secondary study outcomes include economic evaluation and costs indicators from the provider perspective, self-reported vaccine confidence and vaccine delay, and the completion rates of 2-dose. Vaccine confidence, defined as public trust in the vaccine safety, importance and effectiveness [[24](https://bmcpublichealth.biomedcentral.com/articles/10.1186/s12889-022-14947-3#ref-CR24)], will be measured using survey items that have been adapted to the local context to assess vaccine confidence in China [[25](https://bmcpublichealth.biomedcentral.com/articles/10.1186/s12889-022-14947-3#ref-CR25), [26](https://bmcpublichealth.biomedcentral.com/articles/10.1186/s12889-022-14947-3#ref-CR26)]. Vaccine delay, defined as individuals have positive intentions to vaccinate but fail to act [[27](https://pubmed.ncbi.nlm.nih.gov/29611455/)]. Program costs will include personnel, facilities, equipment, materials and these will be categorized into start-up, fixed, and variable costs.

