**Statistical analysis**

*Primary analysis*

Descriptive analyses of socio-demographic and vaccination rates by study arms will be conducted. The primary analysis will evaluate the hypothesis that the pay-it-forward arm is more effective than the standard-of-care arm in increasing HPV vaccination. The uptake rates between the pay-it-forward and standard-of-care arms will be compared using generalized linear models with Gaussian distribution and identity link function, and the corresponding 95% confidence intervals were calculated using sandwich variance estimator, reported as adjusted proportion differences, by adjusted for demographic backgrounds (study sites, household income level, education level, marital status and sex of the caregiver)..

*Subgroup analysis*

Subgroup analyses will be conducted using generalized linear models with Gaussian distribution and identity link function to determine whether the main effects on vaccine uptake were related to the following factors: (1) household income levels; (2) study sites; (3) sex of the guardian; (4) highest educational attainment of the participating caregiver, (5) age of caregivers, (6) awareness of HPV vaccine.

*Secondary analysis*

We employed a micro-costing method to evaluate the financial cost of implementing HPV vaccination under the two intervention strategies from the health provider’s perspective (Sichuan Department of Health). Cost for each program element will be collected, including personnel, materials, equipment and facilities. Pay-it-forward participant donations will be summarized and the fraction of the total cost of vaccination covered by pay-it-forward donation will be calculated. Mean donations by study site will be calculated and donation distribution by study site will be examined.

Vaccine postponement and vaccine confidence will be summarized using descriptive statistics and will be compared between the two arms. The completion rates of 2-dose HPV vaccination will be compared between the two arms. Comparisons between the 2 arms will be assessed with χ^2^ test, regression analyses, and 95% CIs will be calculated. All statistical tests will be two-sided, and statistical significance will be defined as *p* < 0.05.

*Risk assessment and management*

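### HPV-vaccine awareness, a subgroup factor, is collected after allocation is revealed, and vaccine delay has no stated time point, denominator or derivation

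*Supplement*

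**What the plan says.** All references are to Protocol Version 3.0 in the Supplement.

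- **Order of steps.** Under Randomization and treatment allocation, written consent comes first, and then "Research assistants will then randomize participants into standard-of-care and pay-it-forward arms using a sealed envelope method". The envelope holds an ID that corresponds to the arm, together with "a QR code for an online questionnaire survey, and postcard messages (pay-it-forward arm only". Under Blinding, "the allocated intervention will be concealed from study participants and research assistants onsite prior to assignment until they open the envelope".
- **The survey.** Under Participation and consent, "All participants will be asked to complete a baseline survey after the consent". It covers sociodemographics, views and behaviour on vaccination, pro-social items and "their intended donation to support vaccination of other individuals (pay-it-forward arm only". Data collection and management describes one online questionnaire, linked by ID to the administrative dose records. Further contact by WeChat is mentioned only as a possibility.
- **Subgroup factor.** The list under Statistical analysis ends with "6) awareness of HPV vaccine". The tracking sheet filled in at enrolment does not record awareness.
- **Delay and confidence.** Both are self-reported secondary outcomes. Under Outcome measures: "Vaccine delay, defined as individuals have positive intentions to vaccinate but fail to act". Under Statistical analysis: "Vaccine postponement and vaccine confidence will be summarized using descriptive statistics and will be compared between the two arms". No assessment time is given for either.
- **Window to act.** Under Interventions, a girl who is absent at recruitment may be vaccinated up to three months later.

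**The concern.** A subgroup factor should be something the intervention cannot have changed. The survey is labelled baseline, but as described it cannot be reached before the envelope is opened. Awareness is thus recorded with the arm known. In the pay-it-forward arm it may also be recorded with postcards in hand that were written to close gaps in knowledge about HPV vaccines. If the allocation moves some caregivers from unaware to aware in one arm only, the two arms within each awareness stratum are no longer comparable. A difference in effect between strata can then appear where none exists.

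Vaccine delay raises a different problem. It combines an intention with a later failure to act, and the time allowed for acting runs well past enrolment. The plan does not say when failure is judged, from which source, or among whom. The analysis section also calls the outcome postponement, without defining that term. The choice of denominator can decide which arm looks better. This matters because reduced delay leads the Supplement's title.

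**Working it through.** **1. Sequence.** Consent → envelope opened (arm ID, survey QR code and, in one arm, postcards) → survey, which has an item for one arm only. Nothing in the text places the survey before randomisation. Whether it comes before or after the pamphlet and the pay-it-forward information is not stated.

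**2. The plan's own figure.** No number in the plan is disputed. The planned uptake of 20% versus 36% is used below, and the sample size that rests on it reproduces: n = (1.960 + 0.842)² × (0.20×0.80 + 0.36×0.64) / 0.16² = 119.7, so 120 per arm.

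**3. Awareness subgroup, illustration only.** None of the following inputs is in the documents except the 16-point difference:
- two thirds of caregivers truly aware;
- standard-care uptake 25% in the aware and 10% in the unaware (overall 0.667×25% + 0.333×10% = 20%);
- a constant true effect of 16 points in both strata;
- a fraction s of unaware pay-it-forward caregivers reporting awareness because of the allocation material, with s from 0.1 to 0.4;
- uptake u among those who switch.

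Apparent effect in the aware = [0.667×0.41 + 0.333×s×u] / [0.667 + 0.333×s] − 0.25.

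Apparent effect in the unaware = [0.26 − s×u] / (1 − s) − 0.10.

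| Those who switch | s | Aware | Unaware |
|---|---|---|---|
| typical of the unaware (u = 0.26) | 0.1 | 15.3 points | 16.0 points |
| typical of the unaware (u = 0.26) | 0.4 | 13.5 points | 16.0 points |
| keener than average (u = 0.50) | 0.1 | 16.4 points | 13.3 points |
| keener than average (u = 0.50) | 0.4 | 17.5 points | 0 points |

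True awareness was also varied from 50% to 80%, and a second pair of standard-care uptakes (30% and 5%) was tried. Over all these settings the apparent effect ran from 8.9 to 18.6 points in the aware and from −3.3 to 16 points in the unaware. The bias can go either way. With no switching (s = 0) both strata return 16.

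**4. Direction of delay, illustration only.** Put each girl in one of three groups: vaccinated (U), intends but unvaccinated (D), does not intend (R). Count every vaccinated girl as having intended. Then D = 100 − U − R, so the change in D equals minus the change in U minus the change in R. If uptake rises by 16 points, delay among all randomised girls rises whenever refusal falls by more than 16 points.

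Take an assumed standard-care split of 20 / 50 / 30 and pay-it-forward uptake of 36:

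| Fall in refusal | Pay-it-forward split U / D / R | Delay, all randomised | Delay, intenders only |
|---|---|---|---|
| 0 | 36 / 34 / 30 | 50% vs 34% | 50/70 = 71% vs 34/70 = 49% |
| 16 | 36 / 50 / 14 | 50% vs 50% | 71% vs 50/86 = 58% |
| 20 | 36 / 54 / 10 | 50% vs 54% | 71% vs 54/90 = 60% |

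(Standard care is given first.) In the last row the two denominators give opposite answers from the same data. The intenders-only denominator is itself changed by the intervention, so it is not a neutral choice.

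**The case against.** The strongest reply is that much of this argues from silence.

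- **Survey waves.** The text speaks of questionnaires in the plural and collects WeChat accounts for follow-up. The missing-data section mentions possible gaps in self-reported delay next to a six-month record of loss to follow-up. An undescribed later survey is possible.
- **Delay.** A reader might infer that delay cannot be observed at all. The documents do not support that: no sentence says delay comes from the enrolment form, and survey and dose records are linked by ID, so intention plus the record could yield it. What stands is that no derivation or time point is written.
- **Two uses of one survey.** A reader might also infer that one form cannot supply both subgroup factors and outcomes. That goes too far. Caregiver income, education, sex and age are little affected by allocation, and a randomised comparison of confidence after allocation needs no baseline.
- **Awareness.** Caregivers in both arms have been telephoned and had the trial explained before randomisation, and both get the same pamphlet. The postcards mainly concern timing and choice of vaccine, and pre-test awareness seemed high. The questionnaire is not shown, so the item may have asked about prior knowledge. All this argues for a small bias, but does not put the measurement before allocation.
- **Figures.** The splits in the delay illustration are assumed, and among intenders they favour pay-it-forward. This stands. The illustration shows only that the sign depends on a choice the plan leaves open.

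**Conclusion.** The point holds in a limited form and should be fixed. As written, HPV-vaccine awareness is measured after randomisation with the arm known, so subgroup effects by it can be biased. The size cannot be derived from the documents and may be small. Vaccine delay lacks a time point, a denominator and a derivation, and its direction can depend on the denominator.

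This assumes that the survey described is the one actually used for awareness. If awareness was in fact asked before the envelope was opened, the subgroup concern falls away. First-dose uptake comes from administrative records and is untouched. One of six subgroup factors and the reporting of two secondary outcomes are affected.

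**What to change.** Data collection was complete when Version 3.0 was issued (Trial status), so moving survey items ahead of the envelope is no longer possible. The changes concern analysis and reporting.

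1. Drop awareness from the subgroup factors, or show it only as a post-randomisation, descriptive factor.
2. Where vaccination intention was recorded, derive delay in all randomised participants from that intention plus the administrative first-dose record at three months. Report vaccinated, intends but unvaccinated, and does not intend together by arm, and use one name for the outcome throughout. If intention was not recorded for everyone, say so and give the numbers.
3. State when the survey was actually completed relative to the envelope and the delivery of the intervention. Describe confidence as a single post-allocation measure without a baseline.

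The cost is one exploratory subgroup, a recoded secondary outcome and some wording. Item 2 needs no new data provided that intention was captured, which the visible description of the survey does not confirm.

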**Blinding**

In a behavioral intervention, both participants and people who deliver the treatment know which treatment they are receiving, and it is impossible to conduct a blind trial. But we will adopt several blinding techniques during the process to minimize biases. First, our trial will use an envelope concealment method. The process of generating the sequence of random digits and assembling envelopes is confidential to all on-site research assistants who recruit participants. Second, the allocated intervention will be concealed from study participants and research assistants onsite prior to assignment until they open the envelope. Second, the community health staff coordinator will not know which treatment a participant receives but only help coordinate within the clinic for administering the vaccination after the intervention delivery. Third, both the research assistants and/or community staff coordinator will help collect handwritten messages/donations, but they will be trained to maintain a high degree of consistency and neutrality in the process. Fourth, the allocated intervention (pay-it-forward or standard-of-care) will be blinded to physicians who prescribe an HPV vaccine throughout the process. Finally, the outcome assessors will be blinded from the knowledge of which intervention a participant receives.

**Data collection and management**

Information about vaccine uptake (completion of one dose and two doses respectively) and types of vaccines will be ascertained by clinical administrative data. Survey data will be collected using an online questionnaire. Administrative and survey data will be linked using numerical IDs. Cost data will be collected after we complete the trial. Dependent on the need of extra data for answering the proposed project objectives, participants can be further contacted via WeChat for additional follow- ups after ethical clearance.

**Outcome measures**

*Primary outcome*

The primary outcome of the study will be first-dose HPV vaccine uptake in each arm after the intervention as assessed by administrative records. The choice of HPV vaccines will be dependent on the availability of vaccine products at the selected community health centers, primarily 2v-HPV vaccines.

*Secondary outcomes*

Secondary study outcomes include economic evaluation and costs indicators from the provider perspective, self-reported vaccine confidence and vaccine delay, and the completion rates of 2-dose. Vaccine confidence, defined as public trust in the vaccine safety, importance and effectiveness [[24](https://bmcpublichealth.biomedcentral.com/articles/10.1186/s12889-022-14947-3#ref-CR24)], will be measured using survey items that have been adapted to the local context to assess vaccine confidence in China [[25](https://bmcpublichealth.biomedcentral.com/articles/10.1186/s12889-022-14947-3#ref-CR25), [26](https://bmcpublichealth.biomedcentral.com/articles/10.1186/s12889-022-14947-3#ref-CR26)]. Vaccine delay, defined as individuals have positive intentions to vaccinate but fail to act [[27](https://pubmed.ncbi.nlm.nih.gov/29611455/)]. Program costs will include personnel, facilities, equipment, materials and these will be categorized into start-up, fixed, and variable costs.

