Low HPV vaccination coverage is related to poor availability and affordability, vaccine hesitancy [[4](https://bmcpublichealth.biomedcentral.com/articles/10.1186/s12889-022-14947-3#ref-CR4)], and inappropriate messaging [[5](https://bmcpublichealth.biomedcentral.com/articles/10.1186/s12889-022-14947-3#ref-CR5)]. HPV vaccines are generally not covered by insurances or government programs throughout China except in a few cities [[6](https://bmcpublichealth.biomedcentral.com/articles/10.1186/s12889-022-14947-3#ref-CR6)]. Guangdong Province, Fujian Province, and municipal Ordos and Chengdu provide subsidized HPV vaccination to girls aged 13–14 years old [[7](https://bmcpublichealth.biomedcentral.com/articles/10.1186/s12889-022-14947-3#ref-CR7),[8](https://bmcpublichealth.biomedcentral.com/articles/10.1186/s12889-022-14947-3#ref-CR8),[9](https://bmcpublichealth.biomedcentral.com/articles/10.1186/s12889-022-14947-3#ref-CR9)] and this might be one of the priorities in the country in the next decade. But this initiative leaves an important catch-up age group (e.g., 15–18 years) behind. The domestically produced 2v-HPV vaccine is cheaper and more available, but willingness to vaccinate remain low due to vaccine hesitancy [[4](https://bmcpublichealth.biomedcentral.com/articles/10.1186/s12889-022-14947-3#ref-CR4), [10](https://bmcpublichealth.biomedcentral.com/articles/10.1186/s12889-022-14947-3#ref-CR10), [11](https://bmcpublichealth.biomedcentral.com/articles/10.1186/s12889-022-14947-3#ref-CR11)]. Vaccine hesitancy, defined as the delay in acceptance or refusal of vaccination despite availability of services, is likely associated with minimal community engagement and inappropriate health messaging that focuses on promoting 4v- and 9v-HPV vaccines in the Chinese market. Innovative strategies are urgently needed to address the above issues and improve uptake of HPV vaccines available in the market among the 15–18-year age group.

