**Problem statement**

Our pre-test suggested that, due to the shortage of 4v and 9v-HPV vaccines in the market, the overwhelming majority of caregivers (91.5%) chose to delay their daughter’s HPV vaccination to wait for the above two types of vaccines to become available. This echoed a previous study [[11](https://bmcpublichealth.biomedcentral.com/articles/10.1186/s12889-022-14947-3#ref-CR11)] that there is greater demand for 4v and 9v-HPV vaccines than the currently available supply, but a delay or refusal of 2v-HPV vaccine uptake. A recent cohort study [[23](https://bmcpublichealth.biomedcentral.com/articles/10.1186/s12889-022-14947-3#ref-CR23)] demonstrated that 2v-HPV administered during the age of 12–13 years can reduce 87% of cervical cancer rates and 97% of grade 3 cervical intraepithelial neoplasia (CIN3), but such protection effects would significantly reduce for women receiving an vaccine at an older age, suggesting the importance of vaccination at an earlier age rather than later. The public health problem is therefore refined as how to address vaccine delay and increase *earlier* uptake of HPV vaccines that are currently available in the Chinese market among adolescent girls aged 15–18.

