**Sample size calculation**

Our pre-test data showed that the pay-it-forward arm had an uptake rate of 98% (49/50) compared to 82% (41/50) in the standard-of-care arm. We, therefore, estimate a difference of 16% in vaccine uptake rates between the two arms. But because the current HPV vaccination rate among this population is generally low at around 10%, for the ongoing trial, we conservatively estimate an uptake rate of 20% in the standard-of-care arm and 36% in the pay-it-forward arm rather than the uptake rates in our pre-test. To achieve an 80% power to detect a difference between the two arms, 120 participants are needed respectively in the pay-it-forward and standard-of-care arms. The test statistic used is the two-sided unpooled Z test and calculated by PASS 2021. The significance level of the test is 0.05. Given a non-response and/or dropout rate of 10%, 133 participants for each arm are needed. To allow sub-analyses on secondary outcomes and sub-group analyses, we will increase the sample size by 20% to 160 in each arm (40 from each clinic in each arm), leading to a total of 320 participants.

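### Vaccine delay is a middle category between vaccinated and not intending to vaccinate, so a between-arm difference in it cannot by itself show that delay was reduced

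*Supplement*

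**What the plan says.** All references are to protocol version 3.0 in the Supplement.

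- **Definition.** Outcome measures, secondary outcomes: "Vaccine delay, defined as individuals have positive intentions to vaccinate but fail to act". The same paragraph gives the source as self-report: "self-reported vaccine confidence and vaccine delay, and the completion rates of 2-dose".
- **Analysis.** Statistical analysis, secondary analysis: "Vaccine postponement and vaccine confidence will be summarized using descriptive statistics and will be compared between the two arms". I take postponement to mean the delay outcome, since no other outcome fits. No denominator, time point or separate category for caregivers who do not intend to vaccinate is given.
- **Refusal as a concept.** The Background recognises refusal as a state distinct from delay: "Vaccine hesitancy, defined as the delay in acceptance or refusal of vaccination despite availability of services".
- **Survey.** Participation and consent: "All participants will be asked to complete a baseline survey after the consent". No other survey is scheduled. Under Randomization and treatment allocation, the envelope holding the assignment also holds "a QR code for an online questionnaire survey".
- **Time to act.** Under Interventions (pay-it-forward arm), vaccination may take place the same day or at an appointment up to three months later.
- **Linkage.** Data collection and management says survey and administrative data will be joined by numerical ID.

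**The concern.** An outcome compared between arms should improve when participants move in the wanted direction and worsen when they move the other way. Delay, as defined, does neither reliably. Vaccinated girls and girls whose caregivers do not intend to vaccinate both count as not delayed. The measure therefore improves when an intending caregiver vaccinates and also when one gives up the idea, and it worsens when a refuser is won over but has not yet acted.

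The source of the data adds a second difficulty. The definition has two parts, intention and failure to act. A survey taken at enrolment can record intention. It cannot record whether the caregiver acts over the following three months, so a survey answer alone need not show failure to act.

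What is at stake is the wording of a conclusion. The Problem statement makes addressing delay part of the refined aim, and the Supplement's title already says that the strategy reduced it. A difference in this outcome, read alone, cannot carry that statement.

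**Working it through.** **Inputs**
- Planning uptake: 20% standard of care, 36% pay-it-forward (Sample size calculation).
- Final size: 160 per arm (same section).
- Shares not intending to vaccinate: not given in the documents. Those below are assumptions chosen to show the range of behaviour.

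**The plan's own figure.** The plan states no expected rate, power or sample size for delay. The uptake calculation does reproduce: n = (1.960 + 0.842)² × [0.20 × 0.80 + 0.36 × 0.64] / (0.36 − 0.20)² = 7.849 × 0.3904 / 0.0256 = 119.7, that is 120 per arm as stated. The planning rates are therefore a fair base for illustration.

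**The identity.** Let V be the share with a recorded first dose, D the share unvaccinated but intending, and R the share unvaccinated and not intending. With no unknowns, V + D + R = 1. Writing Δ for pay-it-forward minus standard of care:

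ΔD = −ΔV − ΔR

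A fall in D equals the rise in uptake only if ΔR = 0. The plan reports ΔV and ΔD but does not fix a common denominator or time point, so ΔR cannot be counted on to follow by subtraction.

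**Illustrations** (standard of care first; counts out of 160; Pearson chi-square without continuity correction)

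| Case | V | R (assumed) | D | Delayed | p |
|---|---|---|---|---|---|
| a. Intenders become refusers | 20% / 20% | 20% / 40% | 60% / 40% | 96 / 64 | 0.0003 |
| b. As a, smaller shift | 20% / 20% | 20% / 31% | 60% / 49% | 96 / 78 | 0.043 |
| c. Intenders vaccinate | 20% / 36% | 20% / 20% | 60% / 44% | 96 / 70 | 0.004 |
| d. Uptake rises, refusal falls | 20% / 36% | 20% / 4% | 60% / 60% | 96 / 96 | 1.0 |

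Cases a and b show significant reductions in delay with no extra girl vaccinated. Case c is a genuine reduction. Case d shows no difference although every shift is favourable. Delay can even rise: with 20 / 50 / 30 (V / D / R, %) under standard of care and 36 / 54 / 10 under pay-it-forward, ΔD = 54 − 50 = +4 points, again with only favourable shifts.

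**Does another denominator help?** Take D / (V + D), the share delayed among those who intend, counting all vaccinated girls as intending.
- Case a: 0.60/0.80 = 75% versus 0.40/0.60 = 67%. Delay still appears to fall with no extra girl vaccinated.
- Case d: 0.60/0.80 = 75% versus 0.60/0.96 = 62.5%. The improvement now shows.

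So it mends case d but not case a. It also conditions on intention, and because the survey code sits inside the allocation envelope, intention may be reported after allocation and be affected by it.

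**Timing.** Intention is asked at enrolment, while action may follow for up to three months. Scoring the definition needs the administrative record at a stated later date. The plan links the two sources but does not say that delay will be derived from both.

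**The case against.** The strongest reply is that delay is secondary and never read alone. First-dose uptake from administrative records is the primary outcome and is reported by arm, so cases a and b would appear beside a null primary result. If delay were expressed over all randomised girls at the same date as uptake, the not-intending share would follow by subtraction. It is also hard to see why a subsidised dose with encouraging postcards would turn intenders into refusers, and the documents offer no evidence that it does. All of this stands. It limits the harm and makes case a an illustration of what the definition allows, not a prediction. It does not remove the need to fix the denominator and the joint reading, and case d needs no harmful effect at all.

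A reader might infer more than the documents support:

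- *That the pre-test contradicts itself.* The Problem statement says "the overwhelming majority of caregivers (91.5%) chose to delay", while the Sample size calculation says "the pay-it-forward arm had an uptake rate of 98% (49/50) compared to 82% (41/50) in the standard-of-care arm", that is 49 + 41 = 90 of 100 vaccinated. If both described the same 100 girls at the same time, at least 91.5 + 90 − 100 = 81.5% would be both delaying and vaccinated. But the 91.5% has no stated denominator or timing and is not a whole count out of 100. It concerns waiting for scarce 4v and 9v vaccine, and Types of HPV vaccines says that 9v was reserved for pre-test participants. Earlier waiting followed by vaccination is compatible with both figures.
- *That the trial's survey item records past waiting.* The questionnaire is not reproduced, so its wording cannot be judged.
- *That adopting the term delay in place of hesitancy is itself a fault.* It is a declared change between versions, and the Problem statement openly narrows the aim to delay.
- *That the plan has no measure bearing on earlier uptake.* In the Problem statement, earlier means vaccinating at a younger age with what is available. First-dose uptake within the trial bears on that.

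**Conclusion.** The point holds in limited form. A between-arm difference in delay, as defined, has no fixed direction of benefit by itself, so it cannot on its own support a claim that delay was reduced. At 160 per arm, an apparent 20-point reduction is possible with equal uptake, and no difference is possible with a 16-point gain in uptake and a 16-point fall in refusal. These sizes rest on assumed refusal shares. The direction problem follows from the definition alone.

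The separate weakness, that a survey taken at enrolment cannot show failure to act, rests on that being the only survey the plan describes.

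It would go too far to say that the delay outcome is useless or that the intervention breeds refusal. Read together with recorded uptake and the not-intending share, it can support the claim. The primary analysis is unaffected. The change should be made before a reduction in delay is reported as a finding.

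**What to change.** Replace the stand-alone delay comparison with one status for every randomised girl, derived from the survey and administrative data already linked by ID:

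1. first dose recorded by a fixed time point;
2. unvaccinated at that point, with intention to vaccinate;
3. unvaccinated at that point, without intention to vaccinate;
4. unvaccinated, intention unknown.

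State the time point. The three-month appointment window and the six-month period for recording loss to follow-up are the two that the plan already contains. Report all levels by arm over all randomised girls. Claim reduced delay only when the fall in level 2 is matched by a rise in level 1 and not by a rise in level 3. Say whether intention was reported before or after the envelope was opened.

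The cost is a few sentences and one extra table. No new data are needed, provided that the questionnaire recorded intention (which scoring the plan's own definition already requires) and that the records show dose status at the chosen date. The downsides are an unknown level where intention was not recorded and a delay result that may look less favourable. Trial status says that data collection was complete and analysis under way when version 3.0 was written, so the rule should be dated and, if set after delay was seen by arm, labelled post hoc.
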